## 1. Background & Rationale

*This should comprise a brief description of the proposed study, a description of the population to be studied, the investigational product(s), device(s) or radiation exposure, a summary of findings from non-clinical studies that potentially have clinical significance, and from previous clinical trials that are relevant to the trial. A summary of the known and potential risks and benefits to human subjects should be presented, together with a justification for the choice of route of administration, dosage, dosage regimen, and treatment period(s). This should be supported by appropriate references to the published literature on the disease or condition, its treatment and the use of the study drug for the indication. Data from previous studies as well as any other information that provides background for the trial should be cited. A statement that the trial will be conducted in compliance with the principles of the Declaration of Helsinki (specifying which amendment), the principles of GCP and all (if any) applicable regulatory requirements is essential. It should also be stated that the protocol is to be submitted for approval by an NHS Research Ethics Committee (REC). The name of the Ethics Committee must be stated if the protocol has already been submitted to the Committee.*

Chronic kidney disease (CKD) in children leading to end stage renal disease (ESRD) requiring dialysis and renal transplantation is one of the most important chronic diseases of childhood. At any time there are about 150 children with ESRD requiring regular dialysis in the United Kingdom, with 50-70 new patients commencing dialysis each year [1]. The number of children with CKD being treated in specialist paediatric nephrology units in the UK is not known but is probably 5-10 times more than the prevalent ESRD population. With modern management of chronic kidney disease and advancements in dialysis therapy, an increasing number of children are surviving through childhood and early adulthood. Thereafter, however, heart disease becomes one of the major causes of death in these young adults. The overall risk of cardiac death is about 700-times higher than in age-matched individuals from the normal population [2]. Cardiovascular disease (CVD) accounts for 40% of all deaths in this cohort and often presents as sudden cardiac arrest (not secondary to hyperkalemia or cerebrovascular accidents) [3-5]. Restoration of renal function by transplantation does not eliminate this increased risk and arterial disease in these adults is likely to relate to pre-clinical arterial disease, particularly arterial stiffening and left ventricular hypertrophy (LVH) developing during childhood.

In adult patients without CKD, predictors of CVD events are structural changes in the heart and arteries: LVH, increased intima-media thickening (IMT) and arterial stiffening that are strongly related to elevated blood pressure. These measures of target organ damage are similarly predictive in adults with CKD [6-8]. Arterial stiffness in particular is one of the most important predictors of CVD events. Blood pressure reduction in adults is highly effective at reducing the progression of CKD and CVD events but in later stages of CKD, it is effective only when accompanied by a reduction in stiffness of the arteries [7].

A high proportion of children with CKD already have evidence of target organ damage to heart and arteries. Mitsnefes *et al* [9] report an increase in the prevalence of LVH from 19% to 39% after 2-years of follow up. Small cross-sectional studies have reported increased carotid IMT in children with pre-dialysis CKD [12-16] and in young adults with childhood-onset ESRD [10,11] compared to controls without CKD. The most marked abnormalities have been observed in children with ESRD on dialysis [12,13,17], with longitudinal data in this group suggesting that there is improvement in cIMT post transplantation [16]. Increased arterial stiffness has been reported in children on dialysis [17,18] and in adults with childhood-onset ESRD [19]. In the adult patients stiffness was strongly related to blood pressure. However, other parameters thought to influence arterial stiffness such as parathormone levels, CRP, calcium containing phosphate binders and vitamin D [20-22] were not reported.

Despite a strong association between left ventricular mass, IMT and arterial stiffness with blood pressure in adults with and without CKD and in children without CKD [23], the role of blood pressure in determining target organ damage in children with CKD remains controversial. There are few data relating elevated blood pressure with IMT [16] and arterial stiffness in children with CKD. LVH and arterial stiffness are thought to be determined less by blood pressure and more by other mechanisms such as hyper-parathyroidism leading to myocardial hypertrophy and arterial stiffening through calcification [11-13,17,24].

The relationship of blood pressure with LVH in children with pre-dialysis CKD too remains unclear with the two largest multi-centre observational reports, one from Europe [24,25] and the other from the United States of America [26] showing conflicting relationships. The largest paediatric dataset is from the multi-centre North American 'CKiD study' that recently reported cross sectional data in 198 patients who had a single clinic BP measurement performed together with echocardiography and 24-hour ambulatory BP monitoring studies [26]. They observed LVH in 34% of the 36 subjects with confirmed hypertension (both clinic BP >95th percentile and ambulatory BP >95th percentile), 20% of 75 subjects with elevated ambulatory BP but normal clinic BP ("masked" hypertension) but only 8% of 83 subjects with normal clinic and ambulatory BP. They reported masked and confirmed hypertension to be significant independent predictors of LVH and concluded that casual BP alone was insufficient to predict the presence of LVH in children with CKD.

The multi-centre European trial, the 'ESCAPE' study aimed to evaluate the renoprotective efficacy of intensified blood pressure control in paediatric patients with pre-dialysis CKD. A significant reduction of renal failure progression was observed in patients who had intensified blood pressure control (<50th percentile) as opposed to conventional BP control (50th-95th percentile) with even better results in patients who achieved both a reduction in proteinuria and blood pressure to 'low-normal' 24-hour mean arterial pressure [25]. The ESCAPE study did not compare effects of aggressive versus standard BP control on LV mass or on arterial structure and function. However at baseline they found no association between LVH and BP [24,25]. In the ESCAPE study, LVH in children with CKD was associated with male gender, anaemia, ponderosity, hyperparathyroidism and reduced GFR but not hypertension [24] whilst the CKiD study reported hypertension defined by ambulatory BP monitoring as a significant risk factor [26]. These differences may be because of the difficulties in the measurement of blood pressure and the definition of "hypertension" during childhood as a categorical state with a value of systolic blood pressure above the 95th percentile for the population [23,27].

In our paediatric pre-dialysis CKD population at the Evelina Children's Hospital, we have recently reported on the significant association between LVH and blood pressure (**Figure 1, Appendix 1**) [28]. The mean LV mass index (LVMI) was  $37.8 \pm 9.1 \text{ g/m}^{2.7}$  in a cohort of 49 patients (29 male), aged  $12.6 \text{ y} \pm 3.0$  (mean  $\pm$  sd), with eGFR  $27.1 \pm 12.2 \text{ ml/min/1.73m}^2$ . Despite having clinic BP (CBP) measurements consistently within the currently accepted normal range (below 90th centile) there was a significant difference in BP (both clinic BP [**Figure 2, Appendix 1**] and 24-hour ambulatory BP monitoring) between those with and without LVH. 49% of our subjects were found to have LVH, as defined by recently published age specific LVMI ranges, related to systolic BP values measured both in clinic and by ambulatory BP monitoring. Patients with LVH had consistently higher BP values than those without ( $p < 0.001$ ); although none were overtly hypertensive ( $>95^{\text{th}}$  percentile). Thus, in our own study [28], we have found a strong correlation between systolic BP *within the normal range* and indexed LV mass (**Figure 1**). Similar to the CKiD study [26] we found high prevalence of LVH in subjects with masked hypertension but in contrast with the CKiD study, clinic systolic BP proved to be the strongest predictor of LVM; ambulatory BP did not add further predictive influence.

These data suggest that even in those with blood pressure below the 90th percentile, blood pressure may still be responsible for at least a component of LVH. The association of LVH with systolic BP in the absence of overt hypertension, suggests that current targets for BP control should be re-evaluated in this population. Extrapolation from data in adults with and without CKD and in children without CKD suggest that the same may be true for IMT and arterial stiffness.

Our findings are at variance with the ESCAPE study both with regard to the finding of a positive association of LVH with BP and lack of an association with male gender, anaemia, inflammation, ponderosity or hyperparathyroidism [28]. The strong correlation of blood pressure with LVH in our own population may in part be because all blood pressure measurements were performed by the same observer using auscultation with mercury sphygmomanometer or calibrated aneroid instruments. When using 24-hour ambulatory BP monitoring (ABPM) we (and the CKiD investigators) included all measurements as opposed to only a proportion of measurements (as in the ESCAPE study). We have previously shown that using a subset of the ABPM is likely to introduce significant clinical errors in the interpretation of ABPM [29].

Expert groups and international committees now recommend that, in adult patients with CKD lower blood pressure targets should be achieved than those aimed for general population [30,31]. These blood pressure targets are equivalent to the 50th-75th percentile in the general young adult population. In contra-distinction to practice in adults, until recently, recommendations for children with CKD were to maintain BP below the 90th percentile for the child's age, gender and height [32]. Based on the findings of the ESCAPE study, the European Society of Hypertension now recommend maintaining BP below the 75th percentile primarily to retard progression of renal failure [33]. Our findings of a high prevalence of LVH in children with CKD and BP below the 90th percentile, together with the experience in adults, raises the important question of whether even this target for children with CKD is too high. An additional consideration in children with CKD is the potential importance of central systolic blood pressure. Preliminary observations from ourselves suggest that central relative to peripheral systolic blood pressure is higher in children with CKD as compared to those without CKD. Because of the limitations of cross-sectional association studies, optimal hypertension control can only be answered by a randomised interventional trial. We propose testing the benefit of maintaining blood pressure below the 40th percentile on cardiovascular target organ damage by a randomised controlled trial.

## EXPERIMENTAL DESIGN AND METHODS

### Protocol

**Subjects** (n=150, to give n=120 complete) will be aged 2 to 15 years with CKD stages 1-4 in the last 12 months. Subjects will be eligible to enter the study whilst on anti-hypertensive/s medications irrespective of recent change/s in anti-hypertensive therapy. Detailed inclusion and exclusion criteria are described later in this document under 'Section 3'. Subjects with arterio-venous fistulae, on dialysis or those with a previous kidney transplant at the time of study entry will be excluded. eGFR will be

calculated using the Schwartz formula and CKD staged as per existing definitions [31,32]. Patients who reach end stage renal failure and commence dialysis or receive a kidney transplant will stop participating in the 'randomised controlled trial' but continue to have measurements performed until the end of the study. Informed consent/assent will be obtained from parents and patients (if age applicable) for participation in the study, as per institutional ethics committee approval. A control group (n=120) of age matched children without CKD will be included with all proposed study related investigations to be performed at baseline and at annual intervals. These will be recruited from siblings of study subjects and from a local community using links from a school based liaison project. In addition we aim to recruit a further control group (n=30) of subjects with systolic BP <50th percentile but on no anti-hypertensive medication.

All study related investigations at 'baseline' will be performed just before randomisation. Following enrolment and performance of baseline investigations children with CKD will be randomised to the two arms of the study: aggressive BP control (below the 40th percentile) or standard BP control (between 50th-75th percentile). A minimisation procedure will be used to ensure that patients randomised to the two arms are matched for: age, gender, CKD stage and proteinuria. Children will be recruited over the first 12-months of the study and will therefore have at least 2-years of follow up. Following randomisation all children in whom blood pressure is not to target will be reviewed at 2-4 weekly intervals. Thereafter all children will be monitored at least 4-monthly at the time of routine hospital visits and have clinic BP maintained in the assigned target range over the duration of the study.

Subjects recruited at other centres Subjects recruited in external centres will await 'research study visit' for performance of study related investigations and subsequent randomisation. Thus, any intervention as part of the research study will commence only following baseline investigations. All cardiac and vascular investigations described in this study will be performed by core group of study investigators at the ECH or at participating external centres.

On entry into the study a detailed history will be taken and case records reviewed to determine the cause and duration of CKD, past and family history relevant to CKD/CVD. Ethnicity (self defined by parents) will be recorded. The following measurements/records will be obtained on the first and subsequent visits:

(i) Clinical history, examination and anthropometry

The clinical history will be updated together with details of current medications including hypertensive treatment, phosphate binders and hydroxylated vitamin D. A clinical examination will be performed. Height (stadiometre), weight, body mass index (BMI) and waist circumference will be recorded. Urine and blood biochemistry will be performed on the first and at annual visits.

(ii) Urinalysis

Urine samples will be collected at study entry and at annual review. First morning voids on the three days prior to clinic visit will be required. The patient will keep urine specimens in a home refrigerator at 4 °C before clinic visits. Specimens will be centrifuged to separate the cellular component from the supernatant and stored at -80 °C. A mean value of three Ualb/Ucreat will be recorded.

(iii) Biochemistry

In addition to serum urea, electrolytes creatinine and cystatin C, the following biomarkers related to arterial injury, calcification and ventricular load will be determined:

- a) Arterial injury: lipid profiles (total cholesterol, LDL-cholesterol, HDL-cholesterol, triglycerides and Apolipoprotein-B), homocysteine, high sensitivity CRP.
- b) Arterial calcification: plasma calcium, plasma phosphate and calcium-phosphate product (Ca\*PO4), plasma intact parathyroid hormone (iPTH), FGF23, 25(OH) vit D, 1,25 (OH) vit D, blood haemoglobin (Hb).
- c) Ventricular load: N-terminal pro-B type natriuretic peptide (NT-proBNP).

(iv) Clinic blood pressure and 24-hour ABPM

a) Clinic blood pressure will be taken as the mean of 3 measurements using the appropriate sized cuff and a calibrated aneroid instrument according to current guidelines. All observers will undergo appropriate training including the evaluation of their variation from independent experienced investigators. Normative criteria will be those defined in the Fourth report of the National High Blood Pressure Education Program Working Group in the United States ('Fourth report') [32] and will be expressed as z-scores.

b) 24-hour ABPM studies will be performed in patients > 5 years and > 120 cm using Spacelabs 90217 oscillometric ABP devices (Spacelabs Inc, Redmond, Wash, USA). The performance of 24-hour ABPM is not mandatory. Measurements will be performed once every 30-minute throughout the period of monitoring. Daytime and nighttime periods during each ABP recording will be defined using information in the patient 'ABPM diary card'. An ABPM study will be judged to be of poor quality and excluded if (1) if there are more than 3-hours of interrupted recordings at any time during the 24-hour period; (2) if the duration of ABPM recording is inadequate and less than 20-hours in total, less than 12-hours continuously or does not include any nighttime measurements. All mean ABPM parameters will be analysed as z-scores using the normative limits as per *Wuhl et al* [38]. Nocturnal systolic and diastolic dipping status will be defined as a reduction in nighttime systolic (or diastolic BP) of greater than 10% of the daytime systolic (or diastolic) BP. All ABPM studies will be analysed centrally at the ECH.

(v) Central blood pressure

Central blood pressure will be estimated from radial tonometry and modified BP measurement using Centron™ BP machine. We are currently performing a validation study to determine which method is most reliable.

(vi) Echocardiography

2D-guided M-mode echocardiography will be performed using images obtained in either parasternal long axis or short axis view of the left ventricle, as recommended by the American Society of Echocardiography [39]. ECHO studies will be performed by trained paediatric echocardiographers using a Philips iE33 ultrasound system (Philips Inc, Andover, Mass, USA). All studies will be stored digitally and analysed by a single investigator ([name]) who will be blinded to the medical history. Left ventricular mass will be calculated using the Devereux equation [40]. Left ventricular mass varies widely across the paediatric age range, therefore to allow standardisation it is usually expressed as left ventricular mass index (LVMI). We will use LVMI (LVM divided by height in meters raised to allometric power of 2.7 [ $\text{g}/\text{m}^{2.7}$ ]) as a measure of LVH that accounts for body size [41]. LVH will be defined as  $\text{LVMI} \geq 95\text{th}$  percentile using age-specific reference intervals for normal children [42], where appropriate, we will also calculate left ventricular mass for height z-scores [43]. Relative wall thickness (RWT) will be measured to assess the left ventricular geometry. Patients with increased LVMI ( $\geq 95\text{th}$  percentile) and elevated RWT ( $\geq 0.41$ ), have concentric LVH; with increased LVMI ( $\geq 95\text{th}$  percentile) and normal RWT ( $< 0.41$ ) have eccentric LVH; and those with normal LVMI ( $< 95\text{th}$  percentile) and elevated RWT ( $\geq 0.41$ ) have concentric remodelling. Shortening fraction will be calculated to estimate the LV systolic function. Diastolic function will be assessed by pulsed Doppler interrogation of mitral valve inflow and tissue velocity imaging interrogation at the level of the mitral valve annulus both at the septum and left ventricular free wall [44]. The mitral valve E/e' ratio will be used as a surrogate for filling pressures. Cross sectional images in both four chambers and multiple short axis views will be obtained to permit analysis of myocardial rotation and torsion using two dimensional strain ("speckle tracking") techniques.

(vii) Carotid intima-media thickness

High resolution ultrasound (Linear transducer for iE33 (15-6MHz) will be used to obtain images of the common carotid artery. Mean common carotid intima-media thickness (cIMT) will be assessed using automated software (Medical Imaging Applications LLC, Iowa, USA) from digitized images obtained in diastole of the near and far walls of the both common carotid arteries 1-2 cm proximal to the flow divider [45,46]. This method is recognized as one of the most robust measures of IMT since the

reproducibility of common carotid IMT measurements is higher than that of other segments [47], and in most studies to date additional measurements from the bifurcation and internal carotid have not improved the predictive value of IMT [48,49].

(viii) Arterial stiffness

Arterial stiffness will be determined by measuring carotid-femoral pulse wave velocity (PWV) in children able to co-operate with this measurement and by measuring arm-thigh PWV in all subjects. Carotid-femoral PWV will be determined using the SphygmoCor system (Atcor medical, Australia) in which ECG referenced sequential carotid and femoral applanation tonometry is performed. This is usually well tolerated in children but some children are unable to keep still during carotid tonometry. An alternative technique (Vicorder, Skidmore Medical) employs simultaneous measurement of pulse waveforms from pressure cuffs placed around the arm and thigh. This method is particularly well tolerated in children. Although it is not an accepted standard we have shown that it is highly (correlation coefficient 0.7) correlated with carotid-femoral PWV obtained using the SphygmoCor system.

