| Eccentric LVH n (%)           | 4 (6)                          | 5 (8)                         |
| Concentric LVH n (%)          | 0 (0)                          | 0 (0)                         |

LVEDd, left ventricular end diastolic diameter; LVESd, left ventricular end systolic diameter; IVS, inter-ventricular septum; PW, posterior wall; RWT, relative wall thickness; LVH, left ventricular hypertrophy; LVM, left ventricular mass; LVMI, indexed left ventricular mass.

**Table S3:** Details of reasons for stopping further follow up of eligible randomly assigned study participants in the HOT-KID trial intention to treat population.

|                                                       | Intensive arm
(n=64) | Standard arm
(n=60) | P       |
|-------------------------------------------------------|-------------------------|------------------------|---------|
|                                                       | (A)                     | (B)                    | A vs. B |
| Withdrawn or elected to withdraw from trial           | 18 (28)                 | 10 (17)                | 0.13    |
| (i) Unable to reach BP target despite multiple agents | 2 (3)                   | 0                      |         |
| (ii) ACEi/ARB intolerance                             | 6 (9)                   | 3 (5)                  | 0.36    |
| reduction in glomerular function rate                 | 5                       | 2                      |         |
| dizzy                                                 | 0                       | 1                      |         |
| leg pains                                             | 1                       | 0                      |         |
| (iii) Participant choice/ other reasons               | 7 (11)                  | 4 (6)                  | 0.36    |
| unwilling to come for increased study visits          | 1                       | 1                      |         |
| relocated                                             | 1                       | 1                      |         |
| stopped taking study medication                       | 1                       | 0                      |         |
| changed mind following baseline visit                 | 2                       | 0                      |         |
| commenced on immunosuppressant                        | 1                       | 0                      |         |

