**Blood pressure targets and drug therapy**

Clinic BP measurements performed over a 3-month period immediately prior to entry to study will be used to calculate average Clinic BP percentile. All subjects participating in the study (with or without anti-hypertensive/s) will be randomly assigned to either 'aggressive' or 'standard' BP target study arms. All subjects will have clinic BP maintained in the assigned target range over the duration of the study. Up or down titration of blood pressure during the trial will be performed as per flowcharts in **Appendix 3**. This will be monitored at least 4-monthly at the time of routine hospital visits. Patients already on anti-hypertensive medications at the time of study entry will continue on these or change as per clinical indication. ACEi or ARB's will be the mandatory first line agents. The dose of the agent will be adjusted to achieve the target blood-pressure levels with initial follow up at 2-4 weekly intervals following commencement of medication. The following order of escalation will be used (1) calcium channel blocker (CCB) (2) beta-receptor blocker (3) others such as diuretic or an alpha channel blockers. The preferential use of long acting drugs with once daily dosing would be recommended. This order of escalation will be used unless there are clear clinical indications for other agents. Amendments to the 'BP titration' procedures (**Appendix 3**) will be made if necessary following review of data after 20 subjects.

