## **2.4.3 Analysis**

As outlined above.

(i) Appointment of ‘Data Monitoring Committee’ (DMC). The members of this committee will include independent observers as per routine guidelines. The DMC will review the results of the proposed interim analysis at 1-year following commencement of study.

(ii) Interim analysis will also review data regarding the safety of proposed study arms at 1-year. The results will be reviewed by DMC and used to inform REC and the wider research team.

(iii) Both SPSSv17 and SigmaStat v10 will be used for statistical analysis, in close consultation with statisticians at Kings College London.

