## **3.3 Withdrawal of Subjects**

*Please provide details of when and how to withdraw subjects from the trial or investigational product treatment. It is essential that you specify the type and timing of the data to be collected for withdrawn subjects and indicate whether (and if so, how) withdrawn subjects are to be replaced, as well as arrangements for safety assessment follow-up of any subjects withdrawn from the trial as a result of (Serious) Adverse Events.*

- i. Subjects will be withdrawn if they are unable to tolerate the performance of study related measurements e.g. height, echo or PWV or if they develop concerning adverse effects as a result of ACEi/ ARB's class of anti-hypertensive drug/s used as part of taking part in the study.
- ii. If a subject wishes to withdraw from the study this will be allowed. Identifiable data already collected with consent would be retained and used in the study. No further data or tissue would be collected or any other research procedures carried out on or in relation to the participant.

- iii. In principle we would aim to keep blood and urine specimen and data gathered up to the point that the consent is lost. However as the patients are continually followed up by the clinical team we will be able to determine if the patient wants us to withdraw their data from the study. We will always follow the patient and/or their families wishes.

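### No readable passage ties renal chemistry to the ACEi/ARB titration visits, so GFR falls between annual samples are found only off-schedule and their by-arm count is hard to interpret

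*Combined protocol and SAP*

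**What the plan says.** **Treatment and contact.** Under the protocol heading on blood pressure targets and drug therapy, "ACEi or ARB's will be the mandatory first line agents", with dose adjustment and "initial follow up at 2-4 weekly intervals following commencement of medication". The subjects section adds: "Following randomisation all children in whom blood pressure is not to target will be reviewed at 2-4 weekly intervals". After that, monitoring is at least 4-monthly at routine hospital visits. SAP 1.4 repeats the drug order and the initial 2-4 weekly spacing. Children with CKD stages 1-4 are eligible.

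**Laboratory schedule.** "Urine and blood biochemistry will be performed on the first and at annual visits" (protocol, item (i) on history and examination; repeated in SAP 1.7). The panel includes creatinine, cystatin C and electrolytes. The protocol 2.3 flowchart and SAP Table 1 tick the blood sample at day 1 and at years 1, 2 and 3, and leave 4 and 8 months blank.

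**Withdrawal.** Protocol 3.3 and SAP 1.3 withdraw children "if they develop concerning adverse effects as a result of ACEi/ ARB's class of anti-hypertensive drug/s". No GFR threshold is given. Table S3 lists "reduction in glomerular function rate" as a reason under ACEi/ARB intolerance.

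**Safety review.** Protocol 5.1 has adverse events assessed at each study visit and important expected events actively surveyed, but it lists neither those events nor any laboratory test. The template guidance still printed there asks for tests suited to the treatment, with their times. Section 5.2 restricts reporting to events judged causally related to the drug. Section 2.4.3 says "Interim analysis will also review data regarding the safety of proposed study arms at 1-year", and dates that analysis from commencement of the study. SAP 2.3 plans only a summary of adverse events by arm.

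**The concern.** A fall in GFR is seen only on a blood test. The protocol estimates GFR with the Schwartz formula, which uses creatinine. The withdrawal rule depends on effects of this kind, yet the readable schedule has no blood test between day 1 and year 1, which is when most dose adjustment would be expected.

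Two things are at stake.

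- **The by-arm count of GFR falls found between annual samples, and of the stops they cause.** If these come from unscheduled tests, the count depends on how often a child is seen and tested, and on the judgement of clinicians who know the allocation (SAP 1.5).
- **The 1-year safety review.** It can examine kidney function by arm only if post-baseline results exist by then.

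**Working it through.** **1. The documents' own figure.** Table S3 gives P = 0.36 for ACEi/ARB intolerance, 6/64 against 3/60.

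- Log odds ratio = ln[(6/58)/(3/57)] = ln 1.966 = 0.676.
- SE = sqrt(1/6 + 1/58 + 1/3 + 1/57) = 0.731.
- z = 0.676/0.731 = 0.92, two-sided P = 0.356.

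The figure reproduces. The sub-rows also add up: 5+0+1 = 6 intensive and 2+1+0 = 3 standard.

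**2. Share due to a fall in GFR.** 5/6 intensive, 2/3 standard, so 7/9 = 78% of ACEi/ARB-intolerance stops, and 7/28 = 25% of all stops in the table.

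**3. Schedule against contacts in year 1.**

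| Contact | Blood sample in the readable schedule | Time to next scheduled sample |
|---|---|---|
| Day 1 | Yes | - |
| First titration review, week 2-4 | No | 52-4 = 48 to 52-2 = 50 weeks |
| Month 4 | No | 8 months |
| Month 8 | No | 4 months |
| Year 1 | Yes | - |

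**4. The 1-year review.** Recruitment takes the first 12 months. A child entering at month m has the first follow-up sample at month m+12. At month 12 from study start this holds only for m = 0, so almost no child has a scheduled post-baseline result. If the data cut came L months late and entry were uniform (my assumption), the fraction with a result would be L/12: 8% for L = 1 and 25% for L = 3.

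**5. What the observed split can say.** 5/64 = 7.8% and 2/60 = 3.3%: ratio 2.3, difference 4.5 points, 95% CI -4.7 to 14.0 (Newcombe), Fisher P = 0.44. Power to detect a true difference of that size is about 19%; 80% power would need 411 per arm.

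**6. How far unequal testing could move the ratio.** This is an illustration on assumed figures; the documents give no test counts. Let both arms have the same true risk. Let p be the chance that a fall is found in the arm with fewer contacts, and k the ratio of contacts. The other arm then finds 1-(1-p)^k, and the observed ratio is [1-(1-p)^k]/p.

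| p | k = 1.25 | k = 1.5 | k = 2 |
|---|---|---|---|
| 0.3 | 1.20 | 1.38 | 1.70 |
| 0.5 | 1.16 | 1.29 | 1.50 |
| 0.7 | 1.11 | 1.19 | 1.30 |

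If the intensive arm has more contacts, the intensive-to-standard ratio is 1.1 to 1.7 with no true difference. If the standard arm has more, it is the reciprocal, 1/1.70 = 0.59 to 1/1.11 = 0.90.

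**The case against.** The strongest reply is that a research schedule is not the whole of monitoring. These children stay in specialist care, are seen at least 4-monthly, and protocol 3.3 notes continuing follow-up by the clinical team. The same tables leave clinic BP and medication review blank at 4 and 8 months although the text requires BP monitoring then, so a blank cell does not show that nothing was done. The titration flowcharts (Appendix 3, Figure S2) are not shown and may contain laboratory checks. Section 5.2 counts an abnormal laboratory finding as a possible adverse event and asks for worsening of pre-existing conditions to be reported, and the DMC may meet more often than yearly. All of this stands. It limits the point to what the readable text schedules and what reaches the trial database.

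A reader might infer more than the documents support:

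- **That GFR falls cannot be detected.** A sustained fall would show on the annual sample, and Table S3 records seven.
- **That the lower target inflates the intensive-arm count.** Review every 2-4 weeks applies to any child off target. The standard arm also has a floor, the 50th percentile in the synopsis and the SAP, with titration both up and down. Table S3 gives no dates, test counts or route of detection, so the direction is unknown.
- **That 13 to 26 reviews a year (52/4 to 52/2) pass without a blood test.** That needs a child off target for the whole year; the plan describes the spacing as initial.
- **That no renal comparison by arm is fair.** Annual eGFR is planned at the same times in both arms.

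**Conclusion.** The point holds in a limited form. In the readable text, renal chemistry is scheduled at day 1 and yearly, none is linked to a titration visit, and section 5.1 names no laboratory safety measure. Yet withdrawal depends on ACEi/ARB effects, and 7 of 9 intolerance stops were falls in GFR. Between-sample falls, and the stops they lead to, are therefore counted by an unstated process. Review frequency depends on being off the assigned target, the clinicians are unblinded, only events judged related are reported, and no threshold is set. The 5 against 2 split is too imprecise to support a difference, and without test counts it cannot be separated from a difference in testing in either direction.

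Annual eGFR is free of this timing problem. It can still lose children who stop after a fall. SAP 3.1.1 assumes missing at random, and a model cannot condition on a fall that was never entered in the database.

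The finding that the 1-year review has almost no scheduled chemistry rests on the planned 12-month recruitment and on counting one year from study start. The whole point assumes that the unseen flowcharts add no laboratory checks. If they do, the text and tables still have to agree with them. The primary LVMI result is not shown to be affected, so this is an inexpensive improvement and not a flaw in the main conclusion.

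**What to change.** 1. Reconcile the biochemistry text (protocol item (i), SAP 1.7), both schedule tables and protocol 5.1 with the drug-therapy section, the withdrawal rules (protocol 3.3, SAP 1.3) and the Appendix 3 flowcharts. The clinical team sets the content and timing of any tests; this review proposes none.
2. Enter in the database the creatinine, eGFR and potassium results already taken in routine care, each with its date and current drug.
3. In SAP 2.3, pre-state one numeric definition of a GFR fall. Tabulate falls and resulting stops by arm, with the number of tests per child beside them.
4. Compare eGFR between arms at the common annual visits, and report this separately from the event count.
5. Give these data to the DMC for the 1-year safety review.

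The cost is a protocol amendment, some extra data-entry fields and one more safety table. Where visits have already taken place, items 2 to 4 can still be done from hospital records for periods covered by consent.
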